##### Post-Trial Survey of Participants

All trial participants (intervention and control) will be sent (via email or post based on preference) a post-trial survey about their involvement in the research. Questions drawn from the study participant feedback questionnaire toolkit [37] will explore the adequacy of information about the trial, experiences of participating, motivation to take part in research, understanding of randomisation processes, and perceived value of the study.

#### 4.1.2. Data Monitoring

##### Formal Committee

Behavioural Activation has been established in previous studies as a safe treatment for depression with a low risk of adverse events; therefore, the trial does not require a formal Data and Safety Monitoring Board (DSMB). Trial progress will be monitored through the Trial Steering Committee that is independently chaired.

### 4.2. Safety Monitoring

Participants will complete trial measures at three time-points: baseline (week 0), end of treatment (week 10), and follow-up (week 26). During the assessments, participants will be required to self-report any medical occurrences, GP visits, hospital admissions, or if they have been sick or unwell (physically or mentally) during the trial period. They will also be asked to report any suicidal thoughts or suicide attempts that have occurred.

An SMS will be sent to participants and peer workers every 2 weeks using REDCap (via TWILIO—a third-party web service), asking them to report any adverse events that occurred. The adverse event reporting period spans from the time of consent through to the completion of week-26 assessments. Adverse events will be graded according to the Common Terminology Criteria for Adverse Events (CTCAE) Version 5.0 [38].

Causality of adverse events will be assessed by the principal investigator to determine if there is a possible link with the trial intervention. The trial will cease immediately if there are any suicide attempts or fatalities that are plausibly linked to either the trial intervention or trial procedures. Adverse events will be reported to the trial sponsor and the relevant human research ethics committee.

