#### 2.6.2. Control (Managing Stress on the Farm)

Participants allocated to the control intervention will receive treatment as usual (primary care visits, antidepressant medication if indicated), weekly mood monitoring, and guided self-help (Managing Stress on the Farm), representing the standard first-line treatment option for people with depression. An automated email directing participants to complete their mood rating will be sent weekly along with a reminder SMS sent to their mobile phone. The workbook provides tailored information, practical activities, and links to further resources (including what to do in a crisis) to support the mental health of members of the farming community. A weekly ‘check-in’ addresses some of the attentional issues related to a self-help workbook control intervention.

An attentional control—to address the non-specific effects of the experimental intervention—was discussed as an alternative comparator intervention. Although there are methodological advantages, we did not consider an attentional control to be consistent with our ethical obligation to ensure that participants were receiving standard of care (guided self-help). That said, we acknowledge the potential that this may overestimate the acceptability of the Back-on-Track intervention.

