### 2.11. Sample Size

The intended sample size is 40 participants (approximately 20 in the intervention supported by 10 peer workers and 20 in the control groups). Sample size calculations are not appropriate for feasibility trials, and a sample of 40 is generally considered adequate to establish that a definitive trial is feasible [29].

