### 2.14. Blinding (Masking)

This is a single-blind trial. All research team members will be masked to group allocation with the exception of the Clinical Trials Platform team, who will need visibility of allocation to provide contact details to peer workers and mail resources to participants in the control group. Peer workers will be delivering the intervention and as such will not be masked.

As part of the consent process, a full explanation of the trial design will be given to participants including a description of the Back-on-Track (experimental) and Managing Stress on the Farm self-help workbook (control) interventions. Consequently, participants will not be blind to group allocation (an open-label trial). Awareness of group allocation can impact how participants respond to the intervention they receive. Participants who know they have been allocated to Back-on-Track may have more favourable expectations than those allocated to the Managing Stress on the Farm group, who may feel disappointed. Participants in the trial may assume that Back-on-Track will be better than Managing Stress on the Farm. Telling participants which intervention they will receive may also influence how participants complete outcome assessments. It is also possible that knowledge of treatment allocation may also impact participant compliance and dropout from the study. It will be important when interpreting the outcomes of this feasibility trial to acknowledge the context within which the research was conducted.

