#### 4.4.2. Distress Management Protocol

A stepped approach will be adopted to manage people experiencing distress or thoughts or plans for self-harm during the trial. All members of the research team and peer workers will receive training around the distress protocol. The peer worker programme delivery manual will include a flowchart outlining the distress protocol for ongoing referral. The participant workbook will include a flow chart outlining the process for participants to seek mental health support should distress be experienced outside of meetings with their peer worker, including direction to local supports where available. Participants will also be offered the opportunity to speak with a psychologist if they withdraw from the trial due to heightened distress.

Control group participants will also be sent weekly mood-monitoring checks. The Clinical Trials Platform will be notified if there is a decline in the mood-monitoring score for 2 consecutive weeks or if the score is less than or equal to four for 2 consecutive weeks. The Clinical Trials Platform will notify the trial psychologist, who will contact the participant to assess their mental health and make any necessary referrals.

Researchers and peer workers will follow the process as above when working with young people aged 15 to 17 years. Additionally, when young people express concern about harming themselves, parents or guardians will be informed about the identified risk.

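### Adverse-event prompting may be more sensitive in Back-on-Track, and psychologist contact triggered by mood scores occurs only in controls but is missing from the control description and cost list

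*Protocol article*

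**What the plan says.** **Adverse events.** Under 4.2 Safety Monitoring, "An SMS will be sent to participants and peer workers every 2 weeks using REDCap", "asking them to report any adverse events that occurred". The window is long: "The adverse event reporting period spans from the time of consent through to the completion of week-26 assessments". Participants in both arms also self-report medical occurrences, service contacts and suicidal thoughts or attempts at the scheduled assessments.

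**Where peer workers sit.** They belong to the experimental arm only. Section 2.11 plans "approximately 20 in the intervention supported by 10 peer workers and 20 in the control groups", and section 2.14 states "Peer workers will be delivering the intervention and as such will not be masked".

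**Mood monitoring.** Section 2.6.2 lists it as a control component: "An automated email directing participants to complete their mood rating will be sent weekly along with a reminder SMS". Section 4.4.2 repeats "Control group participants will also be sent weekly mood-monitoring checks" and adds that the Clinical Trials Platform "will be notified if there is a decline in the mood-monitoring score for 2 consecutive weeks", or if the score is four or less for two weeks running. The platform then alerts the trial psychologist, who contacts and assesses the participant and refers where needed.

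**Costs and service use.** Section 2.9 lists control costs as usual care, the self-help materials and automated mood monitoring. It names clinical psychologist time only under peer-worker supervision in Back-on-Track. The same section plans to quantify differences in service use between arms, and section 4 makes patterns of service use a key outcome of the cost-consequence analysis.

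**The concern.** Two things differ between the arms because of how the trial is run, apart from the treatments being compared.

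First, the fortnightly prompt reaches one kind of reporter in the control arm and two kinds in Back-on-Track. If the second kind reports on participants, more of the same underlying events will be captured in Back-on-Track, and a by-arm table would show an excess where there is none.

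Second, a clinical contact triggered by mood scores is built into the control arm alone, yet the sections that define and cost that arm do not mention it. Referrals made at that contact would feed into control service use, and the psychologist's time is in no control cost line. A reader of the results could not tell how much of the control arm's service use the trial's own monitoring had generated.

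**Working it through.** The plan states no adverse-event rate, reporting rate or trigger rate, so there is no figure to reproduce. Both calculations below are illustrations on assumed inputs.

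**1. Adverse-event capture**

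Inputs: two prompted sources in Back-on-Track and one in control (4.2, 2.11, 2.14); end of treatment at week 10 (3.1); reporting to week 26 (4.2). Assumptions: peer workers report participants' events, sources are independent, true rates are equal, and events are spread evenly over time.

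Let q1 be the share of events a participant reports and q2 the share a peer worker reports.

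- Control capture = q1. Back-on-Track capture = 1 − (1 − q1)(1 − q2).
- With q1 = q2 = 0.60 for all 26 weeks: 1 − 0.4 × 0.4 = 0.84. Ratio 0.84 / 0.60 = 1.4.
- If peer-worker reporting stops at week 10: (10 × 0.84 + 16 × 0.60) / 26 = 18.0 / 26 = 0.69. Ratio 0.69 / 0.60 = 1.15.
- For q1 from 0.3 to 0.9 and q2 from 0.1 to 0.5 over the whole period, the ratio runs from 1.01 (q1 = 0.9, q2 = 0.1) to 2.17 (q1 = 0.3, q2 = 0.5).

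If peer workers report only their own events, this ratio is 1.00.

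**2. How often the decline trigger could fire by fluctuation alone**

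Inputs: two successive weekly declines (4.4.2); about 20 controls (2.11). Assumptions: whole-number 0–10 score, mean 6, no true change, 10 weekly ratings, complete response, and any one-point drop counted as a decline. Neither the scale nor the duration of monitoring is stated. The table gives the simulated share of controls with at least one run of two declines (100,000 simulated participants per cell).

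| Week-to-week correlation | SD 1 | SD 1.5 | SD 2 |
|---|---|---|---|
| 0 | 0.39 | 0.53 | 0.60 |
| 0.5 | 0.41 | 0.57 | 0.65 |
| 0.8 | 0.23 | 0.44 | 0.55 |

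The range is 23% to 65%, or 4.6 to 12.9 of 20 controls. Adding the low-score rule raises it to 32% to 79%. Mood improving by 0.2 points a week with SD 1 and independent weeks gives 26% for the decline rule. Results depend on how coarse the scale is: with a continuous score and independent weeks, the exact figure is 1 − 822041/10! = 0.77.

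**3. The three sections side by side**

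| Section | Mood monitoring in control | Psychologist contact in control |
|---|---|---|
| 2.6.2 Control | yes | not mentioned |
| 2.9 Economic Data | costed | not costed |
| 4.4.2 Distress Management | yes | triggered by scores |

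No score-based trigger is described for Back-on-Track. There, escalation runs through the peer worker and the distress flowchart.

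**The case against.** The strongest reply is that much of what one might infer here is not in the text.

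- **A reader might infer that every Back-on-Track participant has two adverse-event reporters.** Section 4.2 does not say so. Peer workers themselves consent to take part in the research (2.4, 2.12.5), so the prompt may concern their own events. This stands, which is why the point is conditional and asks for clarification. Independence is also doubtful, because a peer worker would learn of events mainly from the participant, and scheduled self-report recovers some missed events in both arms.
- **A reader might infer that the stopping or unblinding decisions are biased.** They do not use an arm ratio. The cessation rule in 4.2 works event by event with a causality judgement, and unblinding (2.14.2) is a case review. This also stands: an extra source adds sensitivity to those decisions and does not create a false comparison.
- **A reader might infer that 2.6.2 and 4.4.2 contradict each other, or that the definitive trial will use a different comparator.** A safety escalation may reasonably appear only in the distress section of a condensed article, and the document fixes no comparator for a definitive trial. What remains is an omission that has consequences for 2.9 and section 4.
- **Back-on-Track has its own support.** It has up to ten sessions, peer workers trained in suicide safety and referral, and fortnightly supervision by a clinical psychologist. The distress protocol and the offer of a psychologist after withdrawal for distress cover both arms. This is correct: the claim is only that the score-triggered route exists in one arm.
- **Forms and tables belong in documents not shown.** That is fair for layout. It does not answer the unclear reporting role in 4.2 or the mismatch between 2.6.2, 2.9 and 4.4.2, which lie within this document.

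**Conclusion.** The point holds in a limited form. Peer workers are prompted for adverse events and exist in one arm only. If they report on participants, any by-arm adverse-event summary mixes unequal sources. The direction would be towards more events captured in Back-on-Track. The size is unknown; 1.15 to 1.4 is what a 60% independent capture rate implies, not an estimate. The article announces no formal between-arm adverse-event comparison, so the exposure is to descriptive tables.

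The control-only psychologist contact is the firmer half, because the plan does commit to reporting service use and costs by arm. On the assumed scales it could reach about 5 to 13 of 20 stable controls over 10 ratings through the decline rule alone. Whether the calls change symptoms or other outcomes cannot be told from the document, and the two asymmetries need not push in the same direction. As this is a feasibility trial with no efficacy test, the matter should be corrected but does not undermine the design.

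**What to change.** 1. In 4.2, state whose events peer workers are asked to report: their participants', their own, or both.
2. Record the source of every event (participant SMS, scheduled self-report, peer worker, psychologist contact).
3. Base any by-arm adverse-event summary on the sources common to both arms, namely participant SMS and scheduled self-report. List events known only from a peer worker or only from a psychologist contact separately. All events still go to safety review.
4. Log psychologist contacts and resulting referrals by arm, include them in the control costs, and show them in the service-use reporting.
5. Reconcile 2.6.2, 2.9 and 4.4.2 on what the control arm receives. The content of the distress and stopping rules stays with the clinical leads.

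The cost is one field on the event form, a contact log and a table layout, with no extra staff. The drawback is that the common-source table leaves some Back-on-Track events out of the headline count, although they appear in the separate listing.

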### 4.3. Community Reference Group (CRG)

A Community Reference Group (comprising community members, service providers, and key stakeholders from the three trial communities) will inform strategies for the recruitment and engagement of peer workers and participants. The Community Reference Group will meet monthly for 6 months to provide input on the tailoring of training materials to accurately reflect the farming context, then as required during the trial period to problem solve emerging issues, e.g., difficulties in recruiting peer workers, slower-than-expected participant recruitment rates.

### 4.4. Ethics and Dissemination

#### 4.4.1. Research Ethics Approval

The trial will be conducted in accordance with Good Clinical Practice Guidelines (ICH GCP, https://database.ich.org/sites/default/files/E6_R2_Addendum.pdf accessed on 20 January 2026). The trial was prospectively registered with ACTRN on 23 April 2024. The St Vincent’s Hospital Human Research Ethics Committee (HREC) (Ref: 070/24) reviewed and approved the trial protocol. Trial documents and a copy of the ethics committee approval letter have been reviewed and approved by the La Trobe University HREC (Ref: HREC 070/24), University of South Australia HREC (Ref 206358), Deakin University HREC (Ref 2024-203), and Edith Cowan University HREC (Ref 2024-05841-[name]).

#### 4.4.2. Distress Management Protocol

A stepped approach will be adopted to manage people experiencing distress or thoughts or plans for self-harm during the trial. All members of the research team and peer workers will receive training around the distress protocol. The peer worker programme delivery manual will include a flowchart outlining the distress protocol for ongoing referral. The participant workbook will include a flow chart outlining the process for participants to seek mental health support should distress be experienced outside of meetings with their peer worker, including direction to local supports where available. Participants will also be offered the opportunity to speak with a psychologist if they withdraw from the trial due to heightened distress.

Control group participants will also be sent weekly mood-monitoring checks. The Clinical Trials Platform will be notified if there is a decline in the mood-monitoring score for 2 consecutive weeks or if the score is less than or equal to four for 2 consecutive weeks. The Clinical Trials Platform will notify the trial psychologist, who will contact the participant to assess their mental health and make any necessary referrals.

Researchers and peer workers will follow the process as above when working with young people aged 15 to 17 years. Additionally, when young people express concern about harming themselves, parents or guardians will be informed about the identified risk.

### 4.5. Confidentiality

Trial data will be directly entered into the electronic case record form. There will be a physical log of participant group allocation (participant names, group allocation, and trial number) that will be securely stored at La Trobe University.

Dissemination Policy: The results of the trial will be reported in an open-access peer-reviewed journal. A summary of findings of the trial will also be published on the National Centre for Farmer Health website.

## 5. Conclusions

This feasibility trial will contribute to evidence informing the future design and implementation of mental health support models in Australia’s farming communities, improving access to appropriate and accessible mental health support in an identified at-risk population.

## Figures and Tables

**Table 1 ijerph-23-00199-t001:** Electronic Case Record Form notification schedule.

Day	Content	Format
0	Request to complete outcome measures	Survey link in email notification, SMS reminder
3	Reminder to complete outcome measures (if not completed)	Survey link in email notification, SMS reminder
6	Reminder to complete outcome measures (if not completed)	Survey link in email notification, SMS reminder
8	Notification to researcher to follow up participant by phone if outcome measures not complete	Email notification to researcher

## Data Availability

The original contributions presented in this study are included in the article. Further inquiries can be directed to the corresponding author.

## Abbreviation

WDHS	Western District Health Service
